**Fig. 5 Fig5:**
[figure not shown]
Approach to optimize the enrollment of high-risk STEC infected participants

For all discharged and outpatients, the child will be asked to go to the ED (if required for the hyperhydration arm) for screening (i.e., baseline laboratory testing) and treatment per the institution allocated pathway. If in the conservative fluid management arm, at the discretion of the responsible physician, the child may be managed as an outpatient and consented for research electronically.

#### Targeted outreach activities

To optimize awareness of the embedded pathways at participating sites to optimize both pathway adherence and study awareness to promote recruitment, we will conduct knowledge dissemination activities aimed at the following groups:Physicians (particularly pediatricians, hospitalists, emergency physicians, nephrologists, gastroenterologists, infectious disease) and nurses at the participating center. These strategies will include emails, lectures, seminars, section/department meetings, creation of order sets, and clinical care guidelines.Physicians providing primary care, hospital-based care, and emergency department care in the institution catchment area—through emails, lectures, seminars, section/department meetings, and the sharing of order sets and clinical care guidelines.Medical microbiology laboratories—through direct communication with laboratory directors to optimize diagnostic testing approaches and mechanisms to become notified of positive test results.

## Assignment of interventions: allocation

### Sequence generation {16a}

The EDC will generate the randomized assignment sequence for the hospitals. A geographically stratified approach will be used with sites grouped into six zones based on country and geographic proximity (Fig. 1), with half the hospitals in each zone assigned to each arm. Participating centers will implement the first assigned intervention until a total study target number of patients is reached. Following a simultaneous crossover, in the second phase, centers will implement the second intervention in a similar number of consecutive patients. The crossover point and timing is planned to occur after 24 months of recruitment with the precise date being determined by the EDC based on actual recruitment.

### Concealment mechanism {16b}

Study site allocation was delayed as long as possible to ensure that sites had signed agreements to participate and final study sites had been identified, ethics approval obtained, and study launch confirmed. Site allocation was revealed on May 6, 2022.

### Implementation {16c}

The allocation sequence was generated by the study’s lead biostatistician [name]. Participants will be started on the care pathway by the responsible health care providers. Participants will be enrolled by research team members. As it is a cluster randomized trial, no allocation will occur at the patient level as it is pre-determined for the site.

## Assignment of interventions: blinding

### Who will be blinded {17a}

This will be an unblinded study. Assessment of the primary endpoint, MAKE30, is objective and unlikely to be influenced by lack of blinding. Participating sites will be provided with their allocated pathway that will be embedded into clinical care, thus blinding is not feasible.

### Procedure for unblinding if needed {17b}

This is not applicable as this is an unblinded study.

## Data collection and management

### Plans for assessment and collection of outcomes {18a}

Plan for assessment of study outcomes is summarized in Table 1 and Sect. 12 (Outcomes).

### Plans to promote participant retention and complete follow-up {18b}

Baseline symptom data will be collected from participants; testing, treatment, and outcome data will be extracted from the medical record. A 30-day (± 7 days) evaluation of renal function is required in the small subset of participants who have an elevated creatinine at the time of pathway termination in children who do not require RRT, to determine the MAKE30 primary outcome. This laboratory evaluation is considered standard of care and thus, no specific research follow-up is required.

A participant will be considered lost to follow-up if a 30-day follow-up serum creatinine value is required to assign MAKE30 status, and none is performed as part of clinical care, or the result cannot be obtained. To minimize lost to follow-up, the following actions will be taken by the clinical care team if a participant fails to return to the clinic for the required follow-up:The clinic will attempt to contact the participant. If contact is made, the clinical care team will counsel the participant on the importance of serum creatinine monitoring. If the participant is unable or unwilling to attend the study site phlebotomy laboratory as directed, the site will provide an alternate, more convenient location for serum creatinine testing.If step 1 is unsuccessful, the research team will make every effort to regain contact with the participant, employing, where possible, up to 3 telephone calls and, if necessary, a certified letter to the participant’s last known mailing address or local equivalent methods. This contact will serve to reinforce the importance of clinical follow-up and we will re-connect the participant with the clinical care team.

Non-adherence with the allocated fluid administration protocol by the clinical care team will not impact research data collection and study procedures; we will collect all primary and secondary outcomes data as well as AEs, SAEs, and unanticipated problems (UP) regardless of adherence status. Participants are free to withdraw from the study at any time thereby terminating further data collection. The reason for participant discontinuation or withdrawal will be recorded.

### Data management

Data collection is the responsibility of research team members at participating sites under the supervision of the local site investigator who is responsible for ensuring the accuracy, completeness, legibility, and timeliness of the data reported. The EDC has created paper and electronic data collection forms for utilization and a detailed Manual of Operations (MOO) that describes source documents, instructions for completing the case report forms, and relevant data handing and monitoring procedures.

Research data will be entered into the study’s REDCap database which is password protected and includes internal quality checks built to identify data that are inconsistent, incomplete, or inaccurate. A risk-based monitoring plan details the data monitoring strategy and procedures. All statistical analyses will be coded and conducted independently by two statisticians.

### Confidentiality {27}

Participant confidentiality and privacy is strictly held in trust by the participating investigators, their staff, and the EDC. No information concerning the study or the data will be released to any unauthorized third party without prior written approval of the sponsor. All data entered into the REDCap database will be encrypted and transmitted to the EDC, linked to a unique research identification number, where it will be stored. No identifiable participant information will be transmitted. All biospecimen samples will be linked to research data by a unique research identification number. Personal health information (PHI) will not be shared with any third parties. Research records at local sites will be locked file in a secure room unless being used by research staff, and all computerized information will be maintained on password-protected computers and archived on a secure server. Security measures will be dictated by local regulatory requirements, including but not limited to locked cabinets in locked offices, and 128-bit or greater encryption on secure computers. Only site investigators, research coordinators, and qualified key personnel will have access to these records. Electronic transmission of de-identified records over public networks will be encrypted with virtual point-to-point sessions using SSL or VPN technology. Data will be analyzed and published in aggregated and encrypted form only.

### Plans for collection, laboratory evaluation, and storage of biological specimens for genetic or molecular analysis in this trial/future use {33}

With informed consent, and as approved by local IRBs/REBs, de-identified biological samples will be stored to be used to explore the pathophysiology of HUS in STEC-infected patients and its complications. During, and after the conduct of the study, an individual participant can choose to withdraw consent to have biological specimens stored for future research. A code-link will be created to link biological specimens with clinical data, thereby enabling analyses while maintaining blinding to participant identity. Following study completion, access to study data and/or biospecimens will be determined by the study’s leadership team. IRB/REB approval will be required for all studies involving biospecimens. Genetic testing of blood samples will not be performed.

## Statistical methods

### Statistical methods for primary and secondary outcomes {20a}

Baseline characteristics of subjects will be summarized by intervention group. Counts and proportions will be used for categorical variables and means, standard deviations, medians, and quartiles will be used for numeric variables.

We will adhere to the ITT principle. The primary outcome, the MAKE30, will be compared between children allocated to hyperhydration vs. those allocated to conservative fluid management. We will use logistic regression with generalized estimating equation (GEE) methods to account for clustering at the site level. Fixed model terms will include treatment effect and period effect. Other baseline terms in the model will be age (as a continuous variable), serum creatinine, and hematocrit. These variables have been associated with adverse kidney outcomes in this population. The superiority test of null treatment effect will be carried out at the 0.05 level. Parameter estimates and 95% confidence intervals will be provided for all model terms. Carry-over effect will not be present in our crossover design in the traditional sense as patients themselves, and therefore, their outcomes will only be subject to one type of treatment. The only possible “carryover” effect would be a lack of adherence to the new treatment protocol after the crossover at the site level. We will monitor this closely and its potential effect which would be to reduce power.

The primary outcome, MAKE30, is a composite measure that includes (1) death, (2) new initiation of RRT, and (3) persistent kidney dysfunction. The latter is traditionally defined by a persistent increase in creatinine from a known baseline value at 30-day follow-up. However, most children with STEC-HUS are previously healthy and do not have baseline serum creatinine values available. As such, we will compare 30-day values to estimated, pre-illness values. Although imputation methods have been used previously in critically ill children to estimate baseline serum creatinine values, most of these require patient height. However, as children managed as outpatients under the conservative fluid management strategy will not routinely have height documented, this approach also would be a challenge to our study. Pottel et al. [45], however, established and validated a height-independent equation that performs similarly to height-dependent equations as a screening tool for kidney dysfunction [46, 47]. We will use this approach to calculate estimated creatinine values and will define persistent kidney dysfunction as a 50% increase over these estimated values.

Secondary outcomes will be analyzed in a similar manner as the primary outcome, with the dichotomous outcomes of extrarenal complications and HUS utilizing the same logistic regression model. Only patients without HUS at baseline will be included in the latter analysis. Additional details can be found in the HIKO STEC Statistical Analysis Plan.

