### Outcomes {12}

#### Primary outcome: MAKE30 (major adverse kidney events by 30 days)

Because clinical research evaluating the prevention and treatment of AKI has been hampered by the unclear relationship between acute changes in kidney function and longer-term outcomes, the National Institute of Diabetes and Digestive and Kidney Diseases (NIDDK) [40] workgroup on Clinical Trials in AKI recently recommended the use of the MAKE30, a composite endpoint, for phase III trials related to AKI [25]. It is defined by:Death ORProvision of dialysis ORSustained loss of kidney function (at 30 days) reflected by a 100% [41] increase (i.e., doubling) of serum creatinine from baseline

This outcome will be classified following the completion of data extraction and the 30-day follow-up assessment (time 0, as defined above, is used to calculate the 30-day interval). It will be adjudicated based on laboratory values, chart documentation, and 30-day laboratory results. As baseline creatinine values are rarely available for children, all participants will be assigned a value which will be calculated employing a standardized baseline glomerular filtration rate (GFR = 120 ml/min/1.73m^2^) [42].

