#### Secondary outcomes

These will focus on quantifying other measures of efficacy and safety. They have been selected to provide supportive information about the effect of volume expansion on the primary outcome and the natural history of disease (see Table 1).

**Table 1 Tab1:** Outcomes

Outcome measures			
Type	**Name**	**Time frame**	**Brief descriptions**
Primary	Major adverse kidney events to 30 days (MAKE30)	30 days	MAKE30 is defined as: 1) Death due to any cause censored at 30 days after enrollment OR 2) Provision of RRT, any modality, within 30 days of trial enrollment OR 3) Sustained loss of kidney function (100% increase of serum creatinine from baseline at 30 ± 7 days) Baseline serum creatinine: eGFR (120 ml/min/1.73m^2^) will be used to impute an estimated baseline value. This estimate will be applied to all patients as most patients will not have a baseline value from within the 3 months preceding study 30-day serum creatinine: these will only be required for participants with an elevated value at the time of fluid pathway termination who do not receive RRT

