### Sample size

#### Target study sample size

We estimate the overall study sample size required is 1040. The number to be screened will likely be 25% higher given that some children will be ineligible, and some will decline consent. Preliminary data indicate that the primary outcome event rate in the conservative fluid management arm will be approximately 10%. The study will be powered to detect a 5% absolute reduction (risk ratio 0.5) in the rate of MAKE30 in the hyperhydration arm. Using a conservative estimate of 5–15 subjects per year per site, we used simulated data (R software) to generate a power table (Table 3) for a 20- or 26-site cluster-crossover design under varying underlying intra-class correlation (ICC) values. The table shows that power is not highly dependent upon ICC and that 20 and 26 sites are required for 80% and 90% power, respectively, at the ICC estimated from preliminary data (i.e., 0.106) [16]. We expect very low levels of missing data, as participants with elevated creatinine values at the time of discharge will have laboratory follow-up as part of their standard clinical care. Patients who deteriorate and develop the MAKE30 outcome will be readily identified. Thus, the impact of loss to follow-up on power is expected to be minimal.

**Table 3 Tab3:** Power calculations for the primary outcome

Intraclass correlation coefficient	20 cites (approx. 800 subjects)	26 sites (approx. 1040 subjects)
0.05	82%	89%
0.106^a^	81%	90%
0.15	85%	94%

^a^Estimate from preliminary data [16]

The anticipated HUS rate in the conservative fluid management arm is 17.5%, and the rate of extrarenal complications is 7.5%. Detectable absolute differences for these two outcomes with 80% and 90% power, at approximately the same ICC as estimated for the primary outcome, are provided (Table 4). Here, a conservative Bonferroni correction (alpha = 0.025) is used.

**Table 4 Tab4:** Power calculations for secondary outcomes

Outcome	Power	Detectable difference with 20 sites (*n* = 800)	Detectable difference with 26 sites (*n* = 1040)
Hemolytic uremic syndrome—17.5% in conservative fluid management arm	80%	7.2%	6.3%
	90%	8.1%	7.1%
Extrarenal complications—7.5% in conservative fluid management arm	80%	4.7%	4.1%
	90%	5.2%	4.6%

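### The creatinine component of the primary outcome MAKE30 is defined by a doubling in two places and by a 50% rise in a third, and nothing says which prevails

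*Protocol article*

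**What the plan says.** Three places in the protocol article define or describe the third component of MAKE30.

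- **Primary outcome section under Outcomes {12}.** Sustained loss of kidney function at 30 days is "reflected by a 100% [41] increase (i.e., doubling) of serum creatinine from baseline". For the baseline, "all participants will be assigned a value which will be calculated employing a standardized baseline glomerular filtration rate" of 120 ml/min/1.73m².
- **Table 1 (Outcomes).** The same threshold with a time window: "Sustained loss of kidney function (100% increase of serum creatinine from baseline at 30 ± 7 days". Baseline creatinine is again imputed from an eGFR of 120. A 30-day value is required only if creatinine was elevated when the fluid pathway ended and the child did not receive RRT.
- **Statistical methods for primary and secondary outcomes {20a}.** The same composite is named: "The primary outcome, MAKE30, is a composite measure that includes (1) death, (2) new initiation of RRT, and (3) persistent kidney dysfunction". The text then introduces a height-independent creatinine equation, says "We will use this approach to calculate estimated creatinine values", and states that the trial "will define persistent kidney dysfunction as a 50% increase over these estimated values".

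The statistical methods section refers to the SAP only for additional details. The sample size section gives a control event rate of about 10%, attributed to preliminary data, without saying which threshold produced it.

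**The concern.** A 100% increase and a 50% increase are different rules for the same component of the same primary outcome. The text does not present the 50% rule as a sensitivity or secondary definition, and no sentence ranks the two.

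The trial is unblinded, and the article defends this on the ground that MAKE30 is objective (Outcome justification; Who will be blinded {17a}). That defence needs a single rule fixed in advance. The Discussion also relies on publishing the protocol to limit outcome reporting bias, which it cannot do for this component while two thresholds are published. Finally, Interim analyses {21b} plans two formal efficacy analyses with possible early stopping, and the first uses the primary outcome model. If the rule is not settled by then, a stopping decision could rest on an endpoint that was not uniquely specified.

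**Working it through.** **1. The thresholds side by side.** Let R be the imputed baseline creatinine and C the 30-day value, in a child without death or RRT.

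| 30-day value | Outcomes section and Table 1 (C ≥ 2.0 R) | Statistical methods (C ≥ 1.5 R) |
|---|---|---|
| C < 1.5 R | non-event | non-event |
| 1.5 R ≤ C < 2.0 R | **non-event** | **event** |
| C ≥ 2.0 R | event | event |

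Only the middle row changes. Children who die or receive RRT are events under both rules. For scale only: if GFR is inversely proportional to creatinine (assumption), a baseline of 120 puts the two cut-offs at 120/2 = 60 and 120/1.5 = 80 ml/min/1.73m².

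**2. The plan's own power figure.** Inputs from the sample size section: 10% v 5%, 26 sites, n = 1040 (520 per arm), ICC 0.106. The 0.05 level is from the statistical methods and is taken as two-sided (assumption). A mean of 40 per site gives m = 20 per site and period. With equal within-period and between-period correlation (assumption), the cluster-crossover design effect is

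DE = 1 + (m − 1)·ICC − m·ICC = 1 + 19 × 0.106 − 20 × 0.106 = 0.894.

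Effective n per arm = 520/0.894 = 581.7. With p̄ the mean of the two rates,

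power = Φ{[|p₁ − p₂| − 1.96·√(2p̄(1 − p̄)/n)] / √([p₁(1 − p₁) + p₂(1 − p₂)]/n)}.

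For 10% v 5%: (0.05 − 1.96 × 0.01545)/0.01538 ≈ 1.28, so power = 90.0%, against 90% stated. For 20 sites (400/0.894 per arm) it is 81.1%, against 81% stated. A GEE simulation with treatment and period terms (400 runs per cell) gave 88.8% and 80.5%. The planned power therefore reproduces.

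**3. What the threshold could do to power.** The document does not say how many children fall in the middle row, so these are illustrations. The first two columns of results take 10% as the doubling-based rate and add events under the 50% rule.

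| Points added to control rate | 5-point difference held | Risk ratio 0.5 held |
|---|---|---|
| 0 | 10 v 5: 90.0% | 10 v 5: 90.0% |
| 2 | 12 v 7: 82.9% | 12 v 6: 94.8% |
| 5 | 15 v 10: 73.2% | 15 v 7.5: 98.2% |

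Conversely, if 10% is the rate under the 50% rule and doubling removes 2 or 3 points from the control rate at risk ratio 0.5, power is 82.0% or 76.4%. The sample size section states the effect both as a 5-point reduction and as a risk ratio of 0.5, and these diverge once the control rate moves. The direction is therefore undetermined.

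**4. How large could the middle row be?** The article expects HUS in 17.5% of the control arm (sample size section) and RRT in 60% of HUS cases (Discussion). RRT alone would then give 0.175 × 0.60 = 10.5%, about the whole planned 10%, leaving 17.5 − 10.5 = 7.0% with HUS but no RRT. If children in the middle row come only from that group (assumption), adding 2 points needs 2/7 = 29% of them to lie there, and adding 5 points needs 5/7 = 71%. If half of HUS cases receive RRT, 8.75% remain and 5 points needs 5/8.75 = 57%. The upper end looks high.

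**The case against.** The strongest defence accepts the conflict and limits what follows from it. Doubling appears in the section that describes adjudication and again in Table 1, so the 50% sentence may simply be a leftover, and the SAP, not shown here, may already settle the matter. That lowers the likely harm but does not remove the defect. The article states two explicit numbers for one component, and condensing a longer document explains missing detail, not conflicting values.

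Four stronger readings are tempting, and the document does not support them.

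- *The statistical methods section governs the analysis, so the 50% rule will be used.* Nothing gives it precedence. Choice of threshold after seeing data is a risk here, not something shown to be possible under the SAP.
- *Every child with a 30-day GFR between 60 and 80 changes status.* Children who received RRT or died do not. Under Table 1, a 30-day creatinine is required only for those with an elevated value at pathway end and no RRT. The 60 and 80 also rest on the inverse-proportionality assumption.
- *The baseline is defined in two contradictory ways.* Obtaining a creatinine from a GFR of 120 requires an equation, and the height-independent one may be that equation. The text does not join them, which is an ambiguity and not a proven contradiction.
- *The trial loses power.* That follows only if events are added equally to both arms. With the risk ratio held, power rises. The missing link between the 10% rate and a threshold is detail that may sit in the full protocol or SAP.

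**Conclusion.** The conflict is real and must be fixed: as published, the primary outcome does not classify every child one way. It is confined to the third component, and to children without death or RRT whose 30-day creatinine is at least 1.5 but below 2 times the reference. Their number cannot be derived from the document; its own HUS and RRT figures suggest it may be small. No power or sample-size defect is shown, since the stated 90% reproduces and the illustrative range runs from 73% to 98% depending on assumptions that the document does not settle. The importance lies in prespecification: an unblinded trial with formal interim efficacy analyses needs one written rule before the first look.

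**What to change.** Choose one creatinine threshold and state it identically in the primary outcome section, Table 1 and the statistical methods section. Do this, and align the SAP if needed, before the first interim efficacy analysis. A sensitivity analysis at the other threshold is optional and is not needed to resolve the conflict.

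Two clarifications belong in the same edit:

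- one sentence saying how the baseline GFR of 120 and the height-independent equation combine to give each child's reference creatinine;
- confirmation, in the sample size section, that the 10% control rate refers to the chosen definition.

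The cost is a few sentences of protocol wording. No new data and no change to the sample size are required on the evidence here.

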#### Inclusion criteria

Age 9 months to < 21 yearsShiga toxin 2 (Stx 2)-positive *E. coli* infection OR a history of bloody diarrhea and evidence of STEC infection OR a presumptive diagnosis of HUS in an individual with a history of diarrhea

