#### Exclusion criteria

Presence of advanced HUS, defined by:Hematocrit < 30% ANDPlatelet count < 150 × 10^3^/mm^3^ ANDCreatinine > 2.0 mg/dL (177 µmol/L)i)The presence of only 1 or 2 of these criteria will not result in patient exclusion, regardless of how close the 3rd criterion is to meeting the exclusion criteria.Prior episode of HUS or diagnosis of atypical HUS [36]Chronic disease limiting fluid volumes administered (e.g., impaired kidney, liver, or cardiac function, chronic lung disease)Evidence of anuria (i.e., no urine output for > 24 h)Hypoxemia requiring oxygen therapyHypertensive emergency defined as:Elevated blood pressure above the 99th percentile for age [37]ANDEvidence of neurological change (any of the following)i)Seizureii)Diplopia or blurred visioniii)Severe vomitingiv)HemiplegiaORSevere chest pain with any of the below:i)Cardiomegaly on chest X-RAYii)Left ventricular hypertrophy on electrocardiogram or echocardiogramiii)Pleural effusions on X-ray

7)Greater than or equal to 10 days since onset of diarrhea or if no diarrhea then the onset of other symptoms [19]8)Known pregnancy9)Language barriers impairing appropriate conduct of the study protocol and/or inability to obtain informed consent

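### The HUS row of Table 4 is calculated on all 1040 enrolled children, but the HUS analysis excludes children with HUS at baseline; n and the 17.5% rate should describe the same population

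*Protocol article*

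**What the plan says.** All references are to the protocol article.

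- **Target study sample size.** The planned enrolment is fixed by "We estimate the overall study sample size required is 1040". For the secondary outcomes the section gives "Detectable absolute differences for these two outcomes with 80% and 90% power". The relevant column of Table 4 is headed "Detectable difference with 26 sites (*n* = 1040", and both outcomes share it. The HUS control rate is set by "The anticipated HUS rate in the conservative fluid management arm is 17.5" percent, and the significance level by "Here, a conservative Bonferroni correction (alpha = 0.025) is used". The ICC is taken as about that of the primary outcome, 0.106.
- **Statistical methods for primary and secondary outcomes {20a}.** For the HUS outcome: "Only patients without HUS at baseline will be included in the latter analysis". The HUS entry in Table 1 carries the same restriction.
- **Inclusion criteria.** One route into the trial is "a presumptive diagnosis of HUS in an individual with a history of diarrhea".
- **Exclusion criteria.** Only advanced HUS is excluded. It requires a hematocrit below 30%, platelets below 150 and creatinine above 2.0 mg/dL together, and "The presence of only 1 or 2 of these criteria will not result in patient exclusion".
- **Table 1, HUS definition.** The hematocrit and platelet limits are the same, but creatinine need only exceed the upper reference limit for age.

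**The concern.** A child who meets both blood-count criteria, with creatinine above the age limit but not above 2.0 mg/dL, has HUS by the Table 1 definition. That child is not excluded as advanced HUS, can be enrolled, and is then left out of the HUS analysis. Other sections treat this as expected: the end-of-fluid-protocol criteria provide for HUS that is already present, and the additional analyses list early HUS as a patient category.

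Table 4 makes no allowance for this. The HUS row has the same n as extrarenal complications, an outcome with no such restriction. No section reduces 1040 for HUS or gives an expected share with HUS at entry. The printed sensitivity for one of the two secondary outcomes therefore refers to a larger group than the one analysed. Anyone using the row to judge what a null HUS result could have missed would be using the wrong n, and possibly a control rate for a different population.

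**Working it through.** **Inputs.** From the sample size section: 1040 children, HUS control rate 17.5%, alpha 0.025, ICC 0.106. From the sequence generation section: half the sites in each arm followed by a crossover, so about 520 per arm. Two points are assumed because the article does not state them: the test is two-sided, and the crossover's within-site comparison multiplies the variance by (1 − ICC) = 0.894.

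**Formula.** With p the control rate, d the absolute reduction, q = p − d and n per arm:

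SE = √{0.894 × [p(1 − p) + q(1 − q)] / n}; power = Φ(d/SE − 2.241).

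**Step 1: reproduce Table 4 with everyone included.** For d = 0.063 and n = 520, SE = √{0.894 × (0.1444 + 0.0995)/520} = 0.02047, d/SE = 3.077, and power = Φ(0.836) = 79.8%. Solving for d:

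| 26-site entry | Printed (80% / 90%) | Formula, n = 1040 |
|---|---|---|
| HUS, 17.5% | 6.3 / 7.1 | 6.31 / 7.12 |
| Extrarenal, 7.5% | 4.1 / 4.6 | 4.09 / 4.57 |

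A pooled-variance version gives 6.33/7.14 for HUS. Without the 0.894 factor the unpooled result is 6.64/7.48, which does not match. The printed HUS figures therefore agree with the full 1040. The 20-site entries come out about 0.1 point below the printed values (HUS 7.10/7.99 against 7.2/8.1).

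**Step 2: remove children with HUS at baseline, keeping 17.5%.** Let f be the share with HUS at baseline. It is an assumption throughout. The analysed number is 1040 × (1 − f). For f = 10%, n = 468 per arm: SE at d = 0.063 is 0.02158, d/SE = 2.919, and power = Φ(0.678) = 75.1%.

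| Assumed f | Analysed n | Detectable at 80% / 90% | Power at 6.3 / 7.1 points |
|---|---|---|---|
| 0 | 1040 | 6.3 / 7.1 | 80% / 90% |
| 2% | 1019 | 6.4 / 7.2 | 79% / 89% |
| 5% | 988 | 6.5 / 7.3 | 78% / 88% |
| 10% | 936 | 6.6 / 7.5 | 75% / 86% |
| 20% | 832 | 7.0 / 7.9 | 70% / 82% |

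Below a share of roughly 3.5% to 5%, power drops by no more than about 2 points.

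**Step 3: suppose instead that 17.5% counts HUS already present at entry.** The rate among children at risk is then (0.175 − f)/(1 − f). For f = 5% this is 0.125/0.95 = 13.2%, with 988 analysed.

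- Detectable absolute difference: 5.6 points (80%) and 6.3 points (90%), smaller than printed.
- Same relative reduction: 6.3/17.5 = 36% and 7.1/17.5 = 41%. Applied to 13.2%, these are 4.7 and 5.3 points, with power of about 62% and 75%.

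The direction of the error on Table 4's absolute scale therefore depends on what the 17.5% describes.

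**The case against.** The strongest reply is that the effect may be trivial and its sign is not settled. Several parts of it stand.

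- **The share may be small.** The screening criteria make children identified only through deterioration and transfer ineligible, and the exclusions remove advanced HUS, anuria and diarrhea of 10 days or more. The background puts HUS at 15–20% of children with high-risk infection overall, at a median of about 7.5 days. The presumptive-HUS entry route could raise the share in this sample, but nothing in the article supports any particular value.
- **The 17.5% may already be an at-risk rate.** A reader might infer from the 15–20% range that 17.5% belongs to all infected children. The article does not establish this. The ICC in the sample size section comes from a cohort that the background describes as free of HUS at first presentation. The background also reports, from that cohort, that 17% of those managed as outpatients came back with HUS. The article does not tie the 17.5% to either figure.
- **The method behind Table 4 is not given.** Table 3 came from simulation. The closed-form match is close at 26 sites and slightly off at 20, so it is strong evidence that all 1040 were used, but it does not prove that no other calculation gives these figures.
- **The consequence is limited.** This is a planning statement for a secondary outcome, and a null result would be read mainly from its confidence interval.

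None of this removes the mismatch: the table prints 1040, and the analysis rule leaves out children whom the eligibility rules let in.

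**Conclusion.** The point holds as an inconsistency between the n in one table row and the analysis population. For any baseline-HUS share above zero, the analysed n is below 1040. If 17.5% is the rate among children without HUS at entry, the printed differences are slightly optimistic: by about 0.1 to 0.2 points at shares of 2% to 5%, and by up to about 0.7 to 0.8 points at 20%. These sizes rest on assumed shares, a two-sided test and the 0.894 variance factor also applying to the restricted set.

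A reader might go further and conclude that the stated 80% and 90% power is not delivered. The documents do not support that as a general statement. They give no baseline share, and if 17.5% includes HUS present at entry, power for the printed absolute differences would rise; only power for the same relative reduction would fall. The supported conclusion is that the row's n does not fit its analysis, and that the population behind its control rate is unknown. Primary power in Table 3 is not affected.

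**What to change.** Restate the HUS row of Table 4 on the number expected to be free of HUS at baseline, over a range of shares that includes small ones (for example 2%, 5%, 10% and 20%). State the source of the 17.5% and whether it is the rate among children without HUS at entry. If it is not, replace it with a rate for that group, so that n and rate describe the same children. Say also whether the row is meant to be read as an absolute or a relative difference, since the two move in opposite directions if the rate changes.

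The cost is one table row and a sentence or two of text. Enrolment, eligibility, the analysis model and the primary power calculation stay as they are.
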